### Sample size

The null hypothesis [36] was H_0_: m_1_ = m_2_, and the alternative hypothesis was H_a_: m_1_ = m_2_ + d, where “***d***” is the difference between two means and n_1_ and n_2_ are the sample sizes for the interventional and control groups, such N = n_1 _+ n_2_. The sample size was estimated using the following predictive equation [36]: $\text{n}\;=\;[\text{2}\;{\text{s}}^{\text{2}}\;{\left({\text{Z}}_{\text{1}-\alpha /\text{2}}\;+\;{\text{Z}}_{\text{1}-\beta }\right)}^{\text{2}}]/{\text{d}}^{\text{2}}$, where

“***n***” is the number of participants;“***Z***_***1-α/2***_” is the normal deviate at a level of significance (type I error at 2-sided = 1.96 at 5% level of significance);“***Z***_***1-β***_” is the normal deviate at 1-β% power with β% of type II error (0.84 at 80% statistical power);“***d***” is the expected difference between average changes of PI-NRS from two groups; and“***s***” is the common variance (standard deviation) of PI-NRS means of two groups. “***s***” was calculated according to the following formula [36]: ${\text{s}}^{\text{2}}\;=\;[({\text{n}}_{\text{1}}-\text{1x}\;{{\text{s}}_{\text{1}}}^{\text{2}}\;+\;({\text{n}}_{\text{2}}-\text{1})\;\text{x}\;{{\text{s}}_{\text{2}}}^{\text{2}}]/({\text{n}}_{\text{1}}+{\text{n}}_{\text{2}}-\text{2})$ .

“***d***” and “***s***” values were obtained from a previous South Korean study [37] including 34 patients (17 in the IG and 17 in the CG). The patients in the IG performed exercises using a video-based app system, whereas those in the CG performed exercises using an image- and text- based printout [37]. In-home training was implemented for six weeks in both groups [37]. The NP intensity was measured before and after the intervention via the PI-NRS. Kim and Shin [37] reported that within both groups, the PI-NRS improved significantly after the intervention. At the end of the intervention, PI-NRS’ changes (expressed as means ± standard deviation) for the IG and CG were 2.23 ± 1.85 and 1.65 ± 1.26, respectively (“***d***” is therefore equal to 0.58 (0.58 = 2.23 - 1.65). Based on the aforementioned study [37], where n_1_ = 17, n_2_ = 17, s_1_ = 1.85, s_2_ = 1.26, “***s***^***2***^” is equal to 2.51 [2.51= [(17-1) x 1.85^2^ + (17-1) x 1.26^2^]/(17 + 17-2)].

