The injection of the aforementioned data in the predictive equation gave a sample size of 117 participants. However, since our study involves a finite population (***i.e.,*** a population with a limited number of participant), a correction was applied to the sample size [36]. The number of participants to be included after correction is given by the formula n’ = (N x n)/(N + n), where “ ***n’*** ” represents the corrected sample size, “ ***N*** ” is the size of the finite population (which is 70 office workers in our study), and “ ***n*** ” is the sample size calculated from the standard formula (n = 117). Therefore, the corrected minimum sample size (***n’***) is equal to 44 participants [44 = (70 x 117)/(70 + 117)]. Assuming a 10% absence during the end of the intervention period, 50 participants (25 in each group) were determined to be the amended sample size [50 = 44/ (1–0.1)].

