### Statistical methods

All data will be analyzed using SPSS version 23. The Shapiro-Wilk test will evaluate the normal distribution of quantitative data. If the distribution will be normal and the variances are equal, the quantitative data will be reported as mean ± standard deviation, and 95% confidence interval. Otherwise, data will be expressed as median (interquartile range). Categorical data will be expressed in percentage frequencies. The between-group differences in the mean changes of the outcome measures (PI-NRS, NDI, SF-12, adherence) after intervention will be calculated using repeated measures mixed models with participants from the IG as random effect, and group (IG or CG) and time (baseline, four weeks, and 12 weeks) as fixed effects, and with adjustments for baseline imbalance. The Spearman rank test or Pearson product-moment correlation coefficient analysis will be used to analyze the associations between clinical data and mean changes in the outcome measures. Two-sided statistical significance is set at a p value < 0.05.

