These positive outcomes may be applicable not only to office workers with NP, but also to all NP patients. The app is a new way to treat and monitor patients’ symptoms and evolution, using new technology that facilitates constant patient-therapist communication. The integration of AI allows for dynamic adjustments based on individual progress, preferences, and real-time feedback, making the rehabilitation process more engaging and tailored to the user’s specific needs [38]. Additionally, the user-friendly interface of smartphone apps facilitates easy access to exercises, promoting greater compliance and consistency [39]. External factors such as participant motivation, technical issues with the app, and the required frequency of notifications may influence adherence to smartphone-guided exercises. To address these challenges, interventions should focus on designing user-friendly applications, providing personalized reminders, and incorporating motivational strategies such as feedback or gamification. These approaches have been suggested to improve adherence to technology-based health interventions in similar contexts [40]. Embracing these advancements in technology holds the potential to revolutionize the landscape of rehabilitation self-exercises, offering patients effective and accessible tools to actively participate in their recovery [41]. A key strength of smartphone-guided exercises is their ability to adapt to individual needs and preferences. The app’s personalized features can dynamically adjust exercise intensity, frequency, and duration based on user feedback and progress. By continuously monitoring user performance and providing real-time feedback, the app can optimize the rehabilitation program to maximize its effectiveness. This level of personalization can significantly improve adherence and motivation, leading to better outcomes in the long term [39]. Research has shown that using these tools is effective on pain, function, posture and QoL in office workers with NP [26,42] and in patients with NP in general [43]. Moreover, it has been shown that such an AI-embedded smartphone app increased the time spent on therapeutic exercise; reduced pain levels and decreased the need for other interventions in both NP and back pain [44]. Similarly, significant improvements in these conditions and in shoulder pain after using an AI-assisted health program in office workers has been reported [45]. By implementing interventions reported to have positive impact in NP within the workplace, corporations are testifying of their growing commitment to employee well-being and are anticipating benefits of cost reduction linked with absenteeism and presentism and enhancing productivity linked with a healthier workforce [46]. These interventions are gaining significance in alleviating the impact of a pathology known to occur within a work duration ≥ 5 years in office computer users independently of other risk factors [47]. The use of digital tools may also have the potential to generate positive impact on healthcare quality [48] and on healthcare systems in general by reducing direct costs (***i.e.,*** lowering face-to-face consultations, preventing unnecessary control visits), and indirect costs (***i.e.,*** patient travel, and work leaves) [49]. Findings from this study could directly inform workplace wellness policies by encouraging employers to integrate smartphone-guided exercise programs as cost-effective and accessible interventions to reduce NP among office workers. Such programs could promote regular physical activity, potentially improving productivity and reducing healthcare costs associated with musculoskeletal complaints. Clinically, these findings may support the use of digital health tools as an adjunct to standard care for NP management, aligning with evidence suggesting that technology-based interventions are effective for musculoskeletal disorders [49]. This will highlight their potential for scalable, real-world application in both occupational and healthcare settings.

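### The size of 50 lacks the planned 80% power: a per-arm number is read as a total, then cut by a finite-population correction that does not apply to a between-arm difference

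*Protocol article*

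**What the plan says.** The Sample size section of the protocol article uses the standard formula for comparing two means, n = 2s²(Z₁₋α/₂ + Z₁₋β)²/d². Its inputs are:

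- a significance level given as "type I error at 2-sided = 1.96 at 5% level of significance";
- a power term given as "0.84 at 80% statistical power";
- a difference in mean PI-NRS change of "0.58 = 2.23 - 1.65", and a pooled variance of 2.51. Both come from an earlier two-arm study with 17 patients per group, whose changes "for the IG and CG were 2.23 ± 1.85 and 1.65 ± 1.26, respectively".

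The section reports that these inputs "gave a sample size of 117 participants". Because the site has 70 office workers, it continues, "a correction was applied to the sample size [36"]. The correction is n' = Nn/(N + n) with N = 70, and the section calls the result, 44, the corrected minimum. Allowing for 10% absence, it arrives at 50, or 25 per group.

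The Statistical methods section plans a repeated measures mixed model with adjustment for baseline imbalance. It states that "Two-sided statistical significance is set at a p value < 0.05". It describes no finite-population adjustment of the variance.

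**The concern.** Two steps between the formula and the final size do not follow.

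**Per arm or total.** With the factor 2s² in the numerator, the formula returns the number needed in each arm. The text describes n only as the number of participants, and carries 117 forward as if it were the whole trial.

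**The correction.** A finite-population correction belongs to estimating a quantity of a fixed population, such as its mean, when a large share of that population is sampled. Little is then left unobserved, so the estimate is more precise. A randomised comparison is different: each worker is observed under one intervention only. The difference between arms has variance of about 2s²/m with m people per arm, however many people work at the site.

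The 80% power of the primary comparison in a superiority trial is at stake. If the assumed 0.58-point difference is real, the trial will more often than not miss significance, while its sample-size section implies a four-in-five chance of finding it.

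**Working it through.** **Inputs**, all from the Sample size section: d = 0.58; SDs of change 1.85 and 1.26 with 17 per group; Z values 1.96 and 0.84; N = 70; loss 10%.

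**1. Reproduce the plan's figures.**
- s² = (16 × 1.85² + 16 × 1.26²)/32 = (54.76 + 25.40)/32 = 2.505, stated as 2.51.
- n = 2 × 2.51 × (1.96 + 0.84)²/0.58² = 39.36/0.3364 = 116.99, stated as 117.
- n' = 70 × 117/(70 + 117) = 8190/187 = 43.8, stated as 44.
- 44/0.9 = 48.9, which becomes 50 with equal arms.

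Every arithmetic step reproduces. The faults are in the method.

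**2. What 117 means.** Power of a two-sided 5% t-test with d = 0.58 and s² = 2.51 (noncentral t, standard error √(2s²/m)):
- m = 117 per arm: 80%.
- m = 58.5 per arm (117 in total): 50%.

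So 117 is per arm. The size for 80% power is 2 × 117 = 234 evaluable, or 234/0.9 = 260 randomised.

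**3. What the correction does.** Since n' = 70n/(70 + n), the result stays below 70 for any n. With d = 0.1 and the same variance, n is 3,936 and n' is 69. A formula that lets any difference, however small, be detected with fewer than 70 people is not measuring the precision of a treatment comparison.

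A simulation that repeatedly drew and randomised workers from one fixed population of 70, with a constant effect of 0.58, gave significant results in about 21% of trials at 22 per arm and 23% at 25 per arm. The finite population restores no power.

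**4. What the planned size delivers** (unadjusted t-test, same inputs):

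| Per arm | Standard error | Power for 0.58 | Difference detectable at 80% | 95% CI half-width |
|---|---|---|---|---|
| 22 | 0.478 | 22% | 1.37 | 0.96 |
| 25 | 0.448 | 25% | 1.28 | 0.90 |
| 35 (all 70 workers) | 0.379 | 33% | 1.08 | 0.76 |

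At 22 per arm the detectable difference is 1.37/0.58 = 2.4 times the assumed one.

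**5. Allowing for baseline adjustment.** The SDs are those of change scores. If baseline and follow-up have equal variances and correlation ρ, adjusting for baseline multiplies the change-score variance by (1 + ρ)/2. The protocol gives no ρ, so these values are assumptions:

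| ρ | Variance factor | Power, 22 per arm | Power, 25 per arm |
|---|---|---|---|
| 0.7 | 0.85 | 25% | 28% |
| 0.5 | 0.75 | 28% | 31% |
| 0.3 | 0.65 | 31% | 35% |
| 0 | 0.50 | 39% | 43% |

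For 80% power at 22 per arm, the variance would have to fall to about 18% of the stated value.

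**The case against.** **The planned model is more efficient than a t-test.** This stands in part. The Statistical methods section does plan baseline adjustment, so 22% to 25% describes an unadjusted analysis and must be labelled so. But the sample-size calculation claims no such gain and gives no correlation, and even a correlation of zero leaves power at or below 43%.

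**The correction has a cited source.** A reference for the formula does not show that it applies to a difference between randomised arms, and the only reason the text gives is that the population is finite.

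**The correction is not the whole cause.** This stands. A reader might infer that the correction alone takes power from 80% to 22%. The document's own figures do not support that: reading 117 as a total already lowers power to about 50%, and the correction accounts for the further fall to 22%. Deleting the correction alone would leave 117 in total looking like the size for 80% power.

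**A null result may not be misread.** This also stands. A reader might infer that the protocol intends to treat a non-significant result as showing no difference. It states no such rule, and it already provides for 95% confidence intervals when data are normally distributed.

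**The Discussion sentence is peripheral.** The Discussion says "These positive outcomes may be applicable not only to office workers with NP, but also to all NP patients". This sits badly with a correction that presumes interest only in 70 workers, but it is a hedged remark and the argument does not need it. The correction fails for a randomised difference even if inference stops at this workforce.

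**Conclusion.** The point holds as two stacked method errors. The planned 50 participants (44 evaluable) do not have the 80% power that the calculation is set for. Power for the assumed 0.58 points is about 22% at 22 per arm and 25% at 25 per arm for an unadjusted two-sided 5% t-test. Under an assumed baseline/follow-up correlation of 0.7 to 0.3, baseline adjustment gives about 25% to 31% at 22 per arm.

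The unadjusted figures rest only on the protocol's own difference, variance, significance level and numbers. The adjusted ones also need the assumed correlations and equal variances at both times. Neither set comes close to the plan, so the sample-size statement is wrong as written and should be corrected.

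**What to change.** In the Sample size section:

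1. Delete the finite-population correction and the statement that 44 (50 with loss) is the minimum size.
2. State that 117 is the number per arm, so that 80% power for 0.58 points needs 234 evaluable participants, or 260 randomised at 10% loss.
3. State that the size of 50 is limited by the workforce of 70, not derived from a power target.
4. Report, labelled as unadjusted, the power for 0.58 points (about 22% to 25%), the difference detectable at 80% power (about 1.3 to 1.4 points) and the expected 95% CI half-width (about 0.9 to 1.0 points). If a gain from baseline adjustment is claimed, give the correlation assumed.

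The cost is a rewritten section and a much less favourable stated power. No extra participants and no change to the conduct of the trial are needed.

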## Introduction

### Background and rationale

Professional organizations worldwide are increasingly recognizing the importance of investing in quality assurance measures aligning closely with international standards that emphasize not only the quality of products and services [1], but also the quality of work life (QoWL) [2]. The role of workplace strategies, processes, and environment has been proven in stimulating employee job satisfaction, well-being, organizational effectiveness and overall productivity [3,4]. By adhering to stringent quality assurance directives, professional organizations strive to ensure that workplaces prioritize factors such as ergonomic design, adequate rest intervals, and access to healthcare services, all of which are essential components of promoting a healthy and sustainable work environment [5]. Work-related musculoskeletal disorders are the most common occupational disorders worldwide [6]. Neck pain (NP) is a major health problem in office workers with a one-year prevalence of 58% among data processing workers, and 33% among other office workers in the UK [7], and of 69% in Belgium [8]. Office workers have been reported to have a higher incidence of chronic pain and transition to persistent or recurrent NP over a one-year period [9]. This disorder is responsible of disability, impaired quality of life (QoL) and QoWL, with a great socioeconomic burden [10,11]. Recognizing the prevalence and the burden of this issue in modern office settings, professional organizations are implementing targeted strategies to address concerns and provide necessary support. These interventions may include ergonomic measures to optimize workstation setups, regular breaks, educational initiatives, and exercises [12].

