## Methods: Participants, interventions, and outcomes

### Study setting

The study will be conducted at the University of Monastir (Tunisia). The latter is a public administration having 70 office workers, with an average (minimum-maximum) age of 45 (30–63) years, possessing an average work tenure of 15 years, engaging in eight hours of desk and computer work daily, five days a week.

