### Eligibility criteria

Inclusion criteria will be the presence of a chronic NP lasting for more than three months, and a PI-NRS pain level at baseline assessment ≥ 3. Non-inclusion criteria will be acute NP, specific causes of NP (***e.g.,*** chronic inflammatory diseases), spine trauma or surgery, cervical radiculopathy or myelopathy, and physical therapy treatments in the last six months before baseline assessment.

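### The target of 50 needs 71% of a 70-person workforce to be eligible and to consent, so on the protocol's own prevalence figures it is very unlikely, though not impossible, to be reached

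*Protocol article*

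**What the plan says.** The Study setting section describes one site, "a public administration having 70 office workers". The Sample size section computes n = 117 and reduces it to 44 with a finite-population correction. The N in that correction is the whole staff ("which is 70 office workers in our study"). The 44 is then inflated for 10% loss: "50 participants (25 in each group) were determined to be the amended sample size".

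The Background and rationale section gives the only prevalence figures in the article: a "one-year prevalence of 58% among data processing workers, and 33% among other office workers in the UK", "and of 69% in Belgium". These count neck pain of any kind.

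The Eligibility criteria are narrower. They require "chronic NP lasting for more than three months, and a PI-NRS pain level at baseline assessment" of at least 3. They exclude specific causes, spine trauma or surgery, radiculopathy or myelopathy, and physical therapy in the previous six months. The Recruitment and Informed consent sections add confirmation by a specialist's examination and written consent. The survey that will count cases has not yet been run.

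**The concern.** The target is set as if the whole staff were available to the trial. In fact only workers with chronic, sufficiently painful, non-specific neck pain who agree to take part can be randomised. The share needed is above every prevalence that the protocol cites, and those prevalences already overstate the eligible pool.

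At stake is a figure that the trial relies on. The 50 is presented as a power-based minimum with allowance for loss. If the site yields clearly fewer, the trial falls below its own stated minimum, with no statement of what precision the smaller number buys. The same 70 also drives the finite-population correction, so a count of staff stands in for a count of eligible cases inside the calculation.

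**Working it through.** **Inputs.** From the Sample size section: change scores 2.23 ± 1.85 and 1.65 ± 1.26, 17 per group, d = 0.58, two-sided 5%, 80% power, N = 70, 10% loss. From Background and rationale: prevalences 33%, 58% and 69%. The share of cases that are eligible and consent (the yield) is not given in the document. I assume values from 50% to 100% and show the range.

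**1. The plan's own figure.**
- s² = (16 × 1.85² + 16 × 1.26²)/32 = 2.505, so s = 1.583.
- n = 2 × 2.505 × (1.96 + 0.84)²/0.58² = 116.8, rounded to 117.
- n' = (70 × 117)/(70 + 117) = 43.8, rounded to 44.
- 44/0.9 = 48.9, so 49, or 50 for equal groups.

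The stated chain reproduces.

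**2. Share of the workforce needed.** 50/70 = 71.4%. The 44 before the loss allowance is itself 44/70 = 62.9%.

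**3. Expected cases before any filter.** 70 × 0.33 = 23.1; 70 × 0.58 = 40.6; 70 × 0.69 = 48.3. These are expected counts, not upper limits. Even at 69%, the trial would need 50/48.3 = 1.035 times the expected number of cases.

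**4. Chance of reaching 50.** Treat each worker as independently recruitable with probability q = prevalence × yield. Then P(at least 50) is the upper tail of a binomial(70, q).

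| Prevalence | Yield (assumed) | Expected recruits | P(at least 50) |
|---|---|---|---|
| 69% | 100% | 48.3 | 0.38 |
| 69% | 90% | 43.5 | 0.067 |
| 69% | 80% | 38.6 | 0.004 |
| 69% | 70% | 33.8 | 0.00007 |
| 69% | 50% | 24.1 | below 10⁻⁹ |
| 58% | 100% | 40.6 | 0.014 |
| 58% | 80% | 32.5 | 0.00002 |
| 33% | 100% | 23.1 | below 10⁻¹⁰ |

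At 69% and 80% yield, the chance of recruiting even 44 is 0.12.

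**5. Finite population.** The correction uses N = 70, all staff. With N = 48 (the 69% expectation) the same formula gives (48 × 117)/(48 + 117) = 34.0. The corrected size thus falls as the pool shrinks, whatever difference the trial can detect, so redoing the correction with a smaller N would not repair the plan.

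**6. What plausible numbers buy.** The 95% CI half-width is t × 1.583 × √(2/n per arm). Power is from the noncentral t distribution at d = 0.58, with no loss.

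| Per arm | t | Half-width (points) | Power |
|---|---|---|---|
| 12 | 2.074 | 1.34 | 14% |
| 20 | 2.024 | 1.01 | 20% |
| 25 | 2.011 | 0.90 | 25% |

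Every half-width exceeds the 0.58 difference that the trial is planned to detect.

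**The case against.** The strongest reply is that the prevalences are background epidemiology from the UK and Belgium and were never offered as a recruitment forecast. The site's staff spend eight hours a day at desks and computers and have on average 15 years of service. The Discussion links neck pain to five or more years of office computer use. The local rate could be higher than any cited figure, and the 33% for other office workers may fit this site least well. This stands, and it is why the conclusion is about likelihood.

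A reader might infer that 50 cannot be delivered, or that 23, 41 and 48 are hard limits. The documents do not support that: 50 is below 70, the counts are expectations, and at 69% with full yield 50 or more would still occur about 38% of the time.

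A reader might also blame the low power on the shortfall. That does not hold either. Full enrolment gives about 25%, and going from 25 to 20 per arm costs about four percentage points. The main cause is separate: the formula yields 117 per group, but the protocol treats it as a total and then reduces it.

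Finally, screening yields and shortfall plans are commonly left to a full protocol, and their absence from an article is no finding. That is accepted. The point here is that the stated target does not fit the stated setting, criteria and prevalences.

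**Conclusion.** The point holds as a matter of feasibility and of how the target is presented. The needed share, 71.4%, exceeds all three cited prevalences, and each eligibility and consent step can only lower the yield. On the protocol's figures the chance of reaching 50 is at best 0.38. It falls to 0.067 at an assumed 90% yield and 0.004 at 80%, all at the highest cited prevalence; at the lower two it is 0.014 or less. This rests on the cited rates applying to this site, on assumed yields, and on workers being independent. A much higher local rate of chronic neck pain would change it, but nothing in the document supplies one. Using all 70 workers as the finite population is a further mismatch with the eligibility criteria. The change should be made before recruitment opens.

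**What to change.** In the Sample size section, state the size as all eligible consenting workers at the site. Keep 50 as a ceiling on what is hoped for, and stop presenting it as a power-based minimum.

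Give the expected number as a range with its assumption visible: for example, 24 to 43 at 69% prevalence with 50% to 90% of cases eligible and consenting, and fewer at the lower cited rates. Once the planned survey has counted cases at the site, that count can replace the borrowed prevalence.

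Beside the range, state the 95% CI half-width (about ±1.3 points with 12 per arm, ±1.0 with 20, ±0.9 with 25) and the power at d = 0.58 (about 14%, 20% and 25%). Say that the 25% at full enrolment reflects the sample-size derivation, which needs its own correction. Do not describe the 70 staff as the population of eligible participants.

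The cost is wording and a less favourable stated size and power. No site or participant is added.
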